**Figure 1 figure1:**
[figure not shown]
Information flow between patient, clinician, and integrated mobile health device.

### Aims and Hypotheses

The aims of this study are to (1) examine whether case management augmented by an mHealth device integrated into a youth mental health team can improve treatment outcomes for young people with a severe mental illness and (2) examine whether the mHealth device can predict mental deterioration versus health for those allocated to the integrated arm of the trial. We hypothesize that (1) case management for a severe mental illness enhanced by an mHealth device integrated into a youth mental health team will result in better outcomes than case management with an unintegrated device and (2) physiological data from an mHealth device will identify periods of mental deterioration.

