## Methods

### Overview

The trial design is a parallel-group randomized controlled trial (RCT) predicting the superiority of case management for severe mental illness with an integrated mHealth device over case management with an unintegrated device. It will examine outcomes both between subjects (ie, case management with an integrated vs unintegrated mHealth device) and within subjects (ie, repeated measures of participants with the integrated device to determine if it predicts mental deterioration). The conditions vary regarding whether information from the mHealth device is shared with participants and clinicians *or* with participants alone. Participants will be randomly allocated to either (1) the integrated (unWIRED) condition, where information from the mHealth device is shared with both participant and clinician, or (2) the unintegrated condition, where information from the mHealth device is sent to the participant alone. Participation in the study will last for 6 months. The design and reporting of this study will follow the CONSORT-EHEALTH (Consolidated Standards of Reporting Trials of Electronic and Mobile Health Applications and Online Telehealth) guidelines [23]. This protocol was registered with the Australian New Zealand Clinical Trials Registry (ANZCTR) (ACTRN12620000642987).

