#### Integrated mHealth Device: unWIRED Intervention

Participants will receive case management for their mental illness as well as wearing the Embrace2 device. This device sends physiological measurements to the Empatica Research Portal, which can then be relayed to health service computers for the treating case manager to view. A dashboard generated by the program Splunk [25] provides case managers with information regarding each participant’s arousal, sleep, and activity from the previous day. Splunk captures, indexes, and correlates real-time data and generates graphs, reports, dashboards, and visualizations. The dashboard provides a visualization of the participant’s EDA and activity over a 24-hour period, as well as representing activity through *speed meters*, which present the participant’s level of activity. The program provides password-protected weblinks allowing clinical staff to view the dashboard from their clinical site. Each participant will also have access to activity-based information, which will be transmitted to their mobile phone’s Mate App. Based on the information provided, case managers and/or participants may choose to alter their management plan. For example, periods of high arousal and/or poor sleep may indicate a need for a medication change or a more assertive intervention. Continuous data will be visually inspected for significant deviations in physiological measures and the *speed meters* will be used to alert clinicians of significant change. Physiological information relayed to both the case manager and participant will be regularly reviewed and discussed during team meetings. Where possible, the use of the dashboard will be recorded in electronic medical records. Adherence to the device will be monitored through a portal that shows if the device is being worn and the data are streaming. If there are consecutive days of nonadherence, the research psychologist (SB) will contact the participant to find out the reason for the disconnection and attempt to troubleshoot. For example, the psychologist may ask participants to remember to wear or charge the device and insure it is paired with their phone.

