#### Unintegrated mHealth Device: Control Condition

Participants in the control condition will receive their standard care in addition to being given an Embrace2 to self-monitor their activity levels. This device will provide information to each participant regarding their activity; however, unlike in the integrated condition, information will not be returned to their treating case manager—the device will not be integrated with the mental health team. The device can be used at each participant’s discretion, without prompting or oversight from their case manager.

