#### Trial Administration

Data will be collected from the Embrace2 in a continuous and ongoing manner for all participants. Case management and treatment will continue as per usual in the community mental health services. Case managers of participants in the integrated unWIRED arm will receive training on how to use the mHealth device and dashboard to monitor a participant’s mental state. Research staff will monitor the extent to which there are data uploaded from the device based on the Empatica Research Portal. If unWIRED participants are observed to have minimal adherence over consecutive days, the research psychologist can contact each participant to determine the reason for the disconnection and attempt to restore the device. During the trial, the research psychologist may send EMA text messages to the unWIRED participants to determine stress levels and their responses will be visible on the Empatica Research Portal. EMA messages will be sent according to a schedule and can also be sent manually by the research psychologist. Physiological data from each unWIRED participant’s previous day will be displayed on the Splunk dashboard, showing their activity, rest, and EDA. A link to the dashboard will be provided to case managers so they can view the information on their work computer. Case managers will use the information from the dashboard to enhance their clinical decisions. Clinical staff and participants will be encouraged to discuss data recorded from the device during their meetings and to include this information in their collaborative care plan. Case managers will be provided with a basic manual for interpreting the dashboard; however, a clinical response will be left to their clinical judgement. Throughout the trial administration, clinical staff will be asked to report on their participant’s ongoing functioning and distress, as described in the Assessments of Mental Deterioration section. The research team can provide support to case managers as needed.

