### Power Calculations and Statistical Analysis

The primary outcome for this study is to compare changes in treatment-related outcomes before and after the intervention for participants enrolled in the integrated versus unintegrated conditions. There are currently no trials examining the augmentation of treatment with an mHealth device, so sample size estimations are made using general calculations. Assuming a moderately sized advantage of the integrated (ie, unWIRED) versus unintegrated device on outcomes (effect size=0.5, 80% power, and a 2-tailed α of .05), we will require 63 participants per group.

The RCT component generally compares measures of mental health, distress, and functioning between the conditions, adjusted for baseline scores. For example, this analysis may focus on an intent to treat using a hierarchical linear model (HLM) to test the differential effects of the two treatment conditions, because this method allows the number of observations to vary between participants and handles missing data by calculating estimates of trajectories using maximum likelihood estimation. Fixed effects could be tested for intervention condition and time of assessment. Random effects in the unstructured models provide an index of the relative effects of the treatments over time. Fixed effects parameters may be tested with the Wald test (*t* test, *P*<.05, 2-sided) and 95% confidence intervals. Analyses will focus on the primary outcomes (ie, CGI scores) and secondary outcomes (eg, APQ6, BASIS-24, DASS-21, PSQI, and AQoL-8D) between the unWIRED group and the active control group, with the main outcome points being at the 6-month follow-up relative to baseline. All results are based on estimated mean values derived from HLM analyses. The within-subjects analysis will be comprised of linear fixed effects models using physiological measurements (ie, sleep, activity, and EDA) to predict measures of mental health, distress, and functioning. Baseline variables may be used as covariates when analyzing individual and between-group differences (eg, age, illness severity, treatments, and personality differences). Thematic analysis [38] will be used to examine individual and group qualitative feedback regarding the acceptability of the mHealth device and the unWIRED intervention for participants and case managers; there will be approximately 10-20 participants in the patient and clinician groups.

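### Aim 2 tests the device's predictive value only in the arm where case managers can act on the signal, and leaves out the control arm, whose data are also collected

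*Protocol article*

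**What the plan says.** The population for the prediction aim is stated twice. Aims and Hypotheses gives Aim 2 as to "examine whether the mHealth device can predict mental deterioration versus health for those allocated to the integrated arm of the trial". The Overview of the Methods describes the within-subjects part as "repeated measures of participants with the integrated device to determine if it predicts mental deterioration". No reason for the restriction is given. The Abstract, Hypothesis 2, the Measurements overview and the statistical section describe the prediction analysis without naming an arm, but none of them says that control data will be used.

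In the integrated arm the signal feeds into care by design. Trial Administration says: "Case managers will use the information from the dashboard to enhance their clinical decisions". The description of the unWIRED intervention gives the example that "periods of high arousal and/or poor sleep may indicate a need for a medication change or a more assertive intervention". The predictors in the analysis are those same measures: Power Calculations and Statistical Analysis plans "linear fixed effects models using physiological measurements (ie, sleep, activity, and EDA) to predict measures of mental health, distress, and functioning" and mentions no term for clinician action.

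The control arm wears the same device. Trial Administration states: "Data will be collected from the Embrace2 in a continuous and ongoing manner for all participants". For controls, "information will not be returned to their treating case manager". The section on assessments of mental deterioration sets monthly CGI, SOFAS and chart assessments and does not limit them to one arm.

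**The concern.** The two aims pull against each other in the only arm used for Aim 2. Aim 1 hopes that case managers who see a warning will act and prevent deterioration. Aim 2 then asks, in those same people, whether the warning was followed by deterioration. Each deterioration that is averted after a signal counts against the device's apparent predictive value. A weak or null Aim 2 could come from a device that carries no information or from a team that used its information well, and the planned analysis could not tell these apart.

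The trial already collects the material for a comparison that would help, since predictors and outcomes also exist in an arm without clinician feedback. The Discussion notes that even severely unwell patients are stable more often than they deteriorate. Setting aside half of the participants therefore thins an already sparse set of informative periods. The limitations listed there do not include this one.

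**Working it through.** **Inputs from the protocol.** 63 participants per group, 126 in total, 6 months, monthly ratings, device data in both arms. The protocol gives no deterioration rate, no rate of clinician response and no wear rate, so the values below for these are assumptions.

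**The plan's own figure.** With effect size 0.5, 80% power and two-sided alpha 0.05, n per group = 2 x (1.960 + 0.842)^2 / 0.5^2 = 62.8, that is 63. The stated figure reproduces, but it covers only the between-arm comparison. No figure is stated for Aim 2.

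**Attenuation in the integrated arm.** Assume a monthly deterioration risk of 5% without an abnormal signal and 20% with one. If nobody acts, the risk ratio is 0.20 / 0.05 = 4.0 and the risk difference is 0.15. If care averts a fraction f of deteriorations after a signal, the risk with a signal becomes 0.20 x (1 - f).

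| f (assumed) | Risk with signal | Risk ratio | Risk difference | Loss in risk difference |
|---|---|---|---|---|
| 0 | 0.20 | 4.0 | 0.15 | - |
| 20% | 0.16 | 3.2 | 0.11 | 0.04 / 0.15 = 27% |
| 40% | 0.12 | 2.4 | 0.07 | 0.08 / 0.15 = 53% |

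The planned models are linear, so for a binary deterioration the risk difference is the closer analogue of the slope. If instead only the excess cases (the 15 points) were averted in these fractions, the risk difference would shrink by 20-40%. For continuous scores such as CGI or SOFAS the size would need further assumptions and is not computed here.

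**Share left out.** By participants it is 63 / 126 = 50%. By data volume, with control wear w relative to the integrated arm, it is w / (1 + w): 50% at w = 1, 43% at 0.75, 33% at 0.5 and 20% at 0.25.

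**Precision.** Take the standard error as proportional to 1 / sqrt(effective participants), with the planned 63 as reference.

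- Pooled slope, equal wear: sqrt(63 / 126) = 0.71.
- Pooled slope, half wear in controls: sqrt(63 / 94.5) = 0.82.
- Control slope alone, equal wear: sqrt(63 / 63) = 1.00, no gain.
- Control slope alone, half wear: sqrt(63 / 31.5) = 1.41, less precise than planned.
- Difference between the two slopes, equal wear: sqrt(63 x (1/63 + 1/63)) = 1.41.

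As a rough scale, take six complete ratings per person and independent residuals. The within-person correlation detectable with 80% power is then about 2.8 / sqrt(5n). This gives 0.16 for the planned 63, 0.11 pooled at equal wear, 0.13 pooled at half wear, and 0.22 for the control arm alone at half wear.

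**The case against.** Several stronger readings are tempting, and the documents do not support them.

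- *That the intervention hides the signal.* Case managers may choose to alter management, and the response is left to their judgement. The association is weakened to the extent that they act and the action works. Complete masking is the extreme case. The text also mixes prediction with detection: Hypothesis 2 and the Abstract speak of identifying or detecting periods of deterioration. For same-period detection, averting later events removes cases but does not cancel the association while a person is unwell.
- *That half of the device data goes unused.* Half is exact for participants. For data volume it is an upper bound, because controls use the device at their own "discretion, without prompting or oversight from their case manager", and contact after nonadherence is described only for unWIRED participants.
- *That the control arm is a clean sample and should carry the primary estimate.* Controls see their own activity and may respond to it. If they stop wearing the device when unwell, their slope is biased in another way. As shown above, their slope alone gains no precision. Making it primary is a debatable trade, not a clear improvement.
- *That the plan is faulty for fixing no predictor window, lag or clustering of errors.* An article commonly leaves these to the analysis plan, so their absence here is no finding.

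It can also be argued that the integrated arm is the natural place to study the device, because wear is supported there and EMA is collected only there. That could justify keeping EMA analyses in that arm. It does not explain the restriction for CGI, SOFAS or chart-based outcomes, and the protocol does not offer it as a reason.

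**Conclusion.** The concern holds in a bounded form. The restriction of Aim 2 to the integrated arm is explicit. It places the prediction analysis where the predictors can trigger care, and it omits 63 of 126 participants for whom the same predictors and main outcomes are collected. The direction of the bias, for a signal that precedes deterioration, is towards a weaker association, so a null Aim 2 would be hard to interpret. Its size is unknown: the fall in risk ratio from 4.0 to 3.2-2.4 and the 27-53% loss in risk difference rest wholly on the assumed risks and averted fractions. The precision gain belongs to the pooled slope only. That slope averages an attenuated arm with one free of clinician feedback, so it reduces the bias without removing it. The primary between-arm comparison is not affected.

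**What to change.** Change Aim 2, the Methods overview and the statistical section so that they name the same population, and bring the Abstract and the Measurements overview into line. Suggested wording: *Within-participant models for CGI, SOFAS and other outcomes collected in both arms will use device data from both arms, with terms for arm and for arm by physiology. The slope in each arm and the pooled slope will be reported. The control-arm slope is free of clinician feedback but not of self-monitoring. Analyses that use EMA remain in the integrated arm. Wear time will be reported by arm, and missing wear will be considered as a possible source of bias.*

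The arm-by-physiology term will be imprecise, so a non-significant result should not be read as showing that there is no attenuation.

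The cost is analysis wording only, with no new data, visits or participants. The downside is that control wear is discretionary and has no adherence follow-up, so the control slope may rest on fewer and selectively missing data. Reporting wear time makes this visible but does not correct it.

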## Methods

### Overview

The trial design is a parallel-group randomized controlled trial (RCT) predicting the superiority of case management for severe mental illness with an integrated mHealth device over case management with an unintegrated device. It will examine outcomes both between subjects (ie, case management with an integrated vs unintegrated mHealth device) and within subjects (ie, repeated measures of participants with the integrated device to determine if it predicts mental deterioration). The conditions vary regarding whether information from the mHealth device is shared with participants and clinicians *or* with participants alone. Participants will be randomly allocated to either (1) the integrated (unWIRED) condition, where information from the mHealth device is shared with both participant and clinician, or (2) the unintegrated condition, where information from the mHealth device is sent to the participant alone. Participation in the study will last for 6 months. The design and reporting of this study will follow the CONSORT-EHEALTH (Consolidated Standards of Reporting Trials of Electronic and Mobile Health Applications and Online Telehealth) guidelines [23]. This protocol was registered with the Australian New Zealand Clinical Trials Registry (ANZCTR) (ACTRN12620000642987).

### Participants

The study will recruit 126 youths aged 18-25 years with a severe mental illness drawn from youth community mental health services in Western Sydney and Sydney Local Health Districts in New South Wales (NSW), Australia, where BK, JS, and AH are senior psychiatrists. Admission to these services is determined by participants experiencing moderate to severe mental illness that impairs functioning. All participants at these sites will be receiving case management for their mental illness, including regular medication monitoring and/or psychosocial treatments consistent with Australian and New Zealand College of Psychiatry guidelines. Participants will not be paid; however, they can be reimbursed for costs associated with participation, such as travel expenses or mobile phone credit.

Inclusion criteria are (1) being a current community mental health service patient, (2) aged 18-25 years, (3) having a confirmed diagnosis of serious mental illness, including schizophrenia spectrum disorders, bipolar affective disorder, severe major depressive disorder, anxiety disorder, and/or personality disorder, and (4) having the capacity to consent to the study.

Exclusion criteria are (1) being non-English speaking, (2) having greater than mild developmental disability, and (3) having an inability to comply with either the requirements of informed consent or the treatment protocol.

Substance use will not be an exclusion criterion, as the effects of stress due to substance withdrawal and self-medication are important factors in relapse. It is also important to keep the study population ecologically similar to the clinical population.

### Equipment

The Empatica Embrace2 [24] will be used as the mHealth device in the study. The Embrace2 is an mHealth device that can be worn like a wristwatch. It has a wearable biosensor that captures, stores, and wirelessly transmits EDA and motion data. The Embrace2 is paired to a mobile phone via Bluetooth, where information is displayed on the Mate App (Empatica Inc) of the participant’s phone. The Mate App is a free app developed for the Embrace2 device. Data from the Embrace2 are uploaded to a secure Empatica cloud server. The device will be worn continuously to monitor physiological state, day and night. It requires charging every 48 hours using a USB and dock. In addition to the Embrace2, the young person will need to own a compatible mobile phone that runs on either the Apple iOS or Android operating system. Basic Android phones will be lent to participants who do not have a suitable phone. The mobile phone will have the free Mate App downloaded for the Embrace2 device. The phone can display activity-related information to the participant through the app. The Mate App also allows participants to log *events*, or make digital diary entries, that can be time stamped against their physiological data.

### Interventions

#### Overview

All participants will receive standard treatments, including case management for their severe mental illness. This involves assessment followed by combinations of medication-based and/or psychosocial treatments. There is a strong emphasis on early intervention in these services. Prospective participants are initially assessed by a multidisciplinary team before being admitted according to standard inclusion criteria. The main criterion for admission is that they are experiencing a moderate to severe mental illness that impairs functioning. Participants are assigned a core case manager; however, their treatment is managed within a team of psychiatrists, nurses, psychologists, occupational therapists, and/or social workers. Treatments offered include case management, medication, psychotherapy, cognitive remediation, vocational interventions, and group programs (eg, psychoeducation). After consenting to the trial, participants at these services will be randomly allocated to one of two interventions that vary with respect to who receives information from the mHealth device.

